## Methods and analysis

### Study design

The current study is a prospective, randomized, open-label, multicenter, interventional, superiority clinical trial with a parallel-arm design, and will be conducted at the Yonsei University Health System (YUHS), which includes Severance Hospital, Gangnam Severance Hospital, and Yonsei Severance Hospital. After the startup phase, we will expand the study to other South Korean centers. The study was registered at ClinicalTrials.gov (NCT05753839). This trial complied with Standard Protocol Items: Recommendations for Interventional Trials (SPIRIT) guidelines. The SPIRIT checklist can be found in Additional file 1. All data will be anonymized and collected on structured case reporting forms.

This study will investigate whether upfront or deferred CN improves oncological outcomes (OS and PFS) in patients with synchronous mRCC and ≤ 3 International mRCC Database Consortium (IMDC) risk features compared to immune checkpoint inhibitors (nivolumab plus ipilimumab combination) alone.

To understand the role of CN in immuno-oncology, we will collect and analyze clinical data and samples (tumor tissue, blood, urine, and stool samples).

### Primary endpoint

The primary endpoint is OS (in months) compared between patients receiving upfront CN, deferred CN, and ICIs only.

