### Study timeline

After completing the recruitment procedure, clinical and pathological data were collected (Table 1).

**Table 1 Tab1:** Clinical and pathological data

Clinical data				Pathological data
Baseline	Surgery-related	ICI therapy-related	Oncological outcome	
Age	OR note (including any intraoperative events)	Dosage	Overall survival	Pathological TNM staging
Sex	EBL	Cycle	Progression-free survival	Cell type
Height	Surgical morbidity (according to CDC)	Toxicities (graded by CTCAE v5.0)	Objective response rate (according to RECIST v1.1)	ISUP nuclear grade
Weight		Total administration periods		
BMI		Cause of discontinuation		
BSA				
KPS				
IMDC risk feature				
Clinical TNM staging				
Metastatic sites				

*BMI* body mass index, *BSA* body surface area, *CDC* Clavien–Dindo classification, *CTCAE* Common Terminology Criteria for Adverse Events, *EBL* estimated blood loss, *IMDC* International mRCC Database Consortium, *ISUP* International Society of Urologic Pathologists, *KPS* Karnofsky Performance Status, *OR* operating room, *RECIST* Response Evaluation Criteria for Solid Tumors

A flowchart of the study is shown in Fig. 1. Patients will be evaluated for eligibility for surgery. If they are not eligible for surgery, they will start ICI therapy (induction phase). Then, they will be assessed for whether they are eligible for surgery. If not, they will continue with ICI therapy (maintenance phase) (Group C). If they are eligible for surgery, they will be randomly allocated to the deferred CN group (Group B) or ICIs only. If they are eligible for surgery at the first visit, they will be randomly allocated to the upfront CN Group A (group A) or the deferred CN group (Group B). Patients will be randomly allocated in a 1:1 ratio using a computer-generated allocation sequence by a local project nurse. The randomization will be performed on an institutional basis to prevent bias.

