**Fig. 1 Fig1:**
[figure not shown]
Study flowchart. CN, cytoreductive nephrectomy; IMDC, International mRCC Database Consortium; Ipi, ipilimumab; mRCC, metastatic renal cell carcinoma; Nivo, nivolumab; KPS, Karnofsky performance status

Candidates for CN are patients with good performance status (Karnofsky performance status ≥ 80%) and less than three IMDC risk features and whose primary tumor could be surgically removed. Metastasectomy can be performed when the metastatic sites can be surgically removed. All patients eligible for ICI therapy will receive four cycles of intravenous nivolumab (3 mg/kg) plus ipilimumab (1 mg/kg) every 3 weeks as the induction phase, followed by a response evaluation. After the induction phase, intravenous nivolumab (3 mg/kg) will be administered 6 times every 2 weeks as the maintenance phase, followed by response evaluation. Nivolumab monotherapy will be maintained for a maximum of 2 years for those without adverse side effects. During ICI therapy, adverse events will be evaluated once per cycle. Patients will discontinue ICI therapy when they develop serious adverse events, including grade 3 or worse, according to the Common Terminology Criteria for Adverse Events version 5.0 (CTCAE v 5.0). In the upfront CN group, the induction phase will be within 6 weeks of surgery, whereas in the deferred CN group, surgery will be performed within 6 weeks of the induction phase. The study will be conducted over a period of 5 years.

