### Statistical analysis

Descriptive statistics will be used to assess clinicopathological characteristics. Mean values and standard deviation will be provided for continuous variables, whereas frequency and percentage distributions will be provided for categorical variables. Groups will be compared using the chi-square test for categorical variables and the Student’s *t*-test for continuous variables. The Kaplan–Meier and log-rank test method and log-rank test will be used to estimate and compare OS and PFS. Univariate and multivariate survival analyses will be conducted using the Cox proportional hazards model, which will provide hazard ratios (HRs) with 95% confidence intervals (CI). For subjects without endpoints or who violate the study protocol will be excluded. Statistical analysis will be performed using SPSS software (version 25.0; IBM, Armonk, NY) and R software [V.3.6.2 (http://www.R-project.org)]. The significance level will be set at *P* < 0.05, and all statistical tests will be two-sided.

Microbiome analyses will be conducted using 16S rRNA sequencing to determine the differences in alpha diversity among the three groups by calculating the Shannon, Chao1, and Simpson indices. Beta diversity will be generated using the weighted UniFrac distance and visualized using a principal component analysis plot. Between-group differences were analyzed using multivariate analysis of variance with permutation. Furthermore, subgroup analysis according to the number and location of metastasis will be performed.

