### Adherence with study protocol

Non-adherence with the trial protocol will be reported and will be dropped out from the study.

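### The primary OS comparison groups patients by treatment received, excludes protocol violators and pools two separately randomized deferred-CN cohorts, so it is not a randomized comparison

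*Protocol article*

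**What the plan says.** - **Comparison.** The Primary endpoint section describes OS as "compared between patients receiving upfront CN, deferred CN, and ICIs only".
- **Analysis set.** The Statistical analysis section adds: "For subjects without endpoints or who violate the study protocol will be excluded". The section on adherence says: "Non-adherence with the trial protocol will be reported and will be dropped out from the study". The article names no as-randomized analysis set.
- **Allocation.** Study timeline describes two separate 1:1 randomizations. Patients fit for surgery at the first visit are randomized to A or B. Patients unfit at first are re-assessed after induction, and for them: "If they are eligible for surgery, they will be randomly allocated to the deferred CN group (Group B) or ICIs only". Those still unfit continue on ICIs and are labelled Group C without randomization.
- **Timing.** Induction is four 3-weekly cycles. For the deferred group, the text under Fig. 1 says "surgery will be performed within 6 weeks of the induction phase". Table 3 puts the end of induction at X + 3 months and deferred surgery at X + 4 months.
- **Test.** The "log-rank test will be used to estimate and compare OS and PFS", with no separation by the point at which a patient was randomized. No time origin for OS is given.
- **Sample size.** The trial is sized on A and B pooled (0.66) against C (0.34).

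**The concern.** A patient can receive deferred CN only after surviving induction and the wait for surgery, and remaining operable throughout. A patient in Group A has the operation near the start. If membership of B depends on having had surgery, or on having stayed within the protocol until surgery, B is selected on events after randomization and A is not selected in the same way. Separately, some B patients were randomized at the first visit and others only after reaching the post-induction check. If OS is counted from baseline, the second cohort cannot die in its first 3 months.

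A versus B is the contrast that answers the trial's question about the timing of CN, and this is where the selection acts most directly. The contrast with ICIs only has a different problem: Group C mixes randomized patients with patients who were twice judged unfit for surgery and never randomized.

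**Working it through.** **1. The plan's own figures.** Inputs from Sample size justification: HR 0.37, two-sided alpha 0.05, power 0.80, allocation 0.66/0.34, control hazard 0.53 per year (median 1.3 years), censoring rate 0.1, follow-up 5 years.
- Events (Schoenfeld): (1.96 + 0.842)² / [0.66 × 0.34 × (ln 0.37)²] = 35.4. The plan states 35.
- Event probability per arm: λ/(λ + 0.1) × [1 − exp(−5(λ + 0.1))], which is 0.805 at λ = 0.53 and 0.512 at λ = 0.53 × 0.37. Pooled: 0.34 × 0.805 + 0.66 × 0.512 = 0.611.
- N = 35/0.611 = 57.2. The plan states 57.

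Both figures reproduce, for the pooled A+B versus C contrast.

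**2. The window.** Four cycles × 3 weeks = 12 weeks = 2.8 months. Adding up to 6 weeks gives 18 weeks = 4.1 months. Table 3 rounds these to 3 and 4 months.

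**3. Deaths inside the window at the control hazard.** 1 − exp(−0.53 × 3/12) = 12.4%, and 1 − exp(−0.53 × 4/12) = 16.2%.

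**4. Null simulation.** Exponential survival with the same hazard in every group (median 15.6 months), 200,000 patients per group, 60 months of follow-up, clock from baseline or ICI start. The share of B carrying guaranteed time is not given in the document, so it is varied.

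| Guaranteed time in B | B vs A HR |
|---|---|
| 3 months, 25% of B | 0.96 |
| 3 months, 50% of B | 0.93 |
| 3 months, 75% of B | 0.90 |
| 3 months, all of B | 0.87 |
| 4 months, all of B | 0.83 |

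Removing every death before month 4 from B is equivalent to the last row. When the plan's censoring of 0.1 per year is added, the HR is 0.81.

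**5. The same check against Group C.** As Study timeline describes it, Group C is entered only after the post-induction assessment.

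| Guaranteed time in C | B vs C HR | A+B vs C HR |
|---|---|---|
| All of C reaches 3 months | 1.11 to 0.95 | 1.13 to 1.04 |
| None (for contrast) | 0.93 to 0.83 | 0.97 to 0.91 |

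The first row fits the described flow. The bias against C is then small or reversed, and for the pooled contrast it runs against CN.

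**6. Power for the randomized B versus C contrast.** Assume that half of the 35 events, about 17, arise after the second randomization, which is 1:1. Power = Φ(√(17 × 0.25) × |ln 0.37| − 1.96) = Φ(2.06 × 0.994 − 1.96) = Φ(0.09), about 54%.

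**The case against.** **The as-treated reading rests on one word.** The abstract speaks of random allocation to three groups, and the time origin of OS is something an article may leave to the full protocol. If OS runs from each patient's own randomization and patients are analysed as assigned, there is no immortal time in either B cohort. This stands, and it is why the size above is conditional. It does not remove the point: the exclusion of violators is stated outright, and pooling the two B cohorts follows from the group definitions.

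**Advantage over C.** A reader might infer that deferred CN is favoured over ICIs only as well. Study timeline does not support that, since Group C patients also have to reach the post-induction check. Within the second randomization, only the wait of up to 6 weeks for surgery remains as a source of guaranteed time.

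**Reclassification.** A reader might suppose that B patients who never reach surgery are counted as ICI-only. That would give a null HR of 0.69 and about 16% false positives with 19 per arm. No section says so; violators are excluded or dropped, not moved.

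**Exclusion of early deaths.** A patient who dies before surgery has reached the OS endpoint, and death is neither called a violation nor listed among the dropout criteria. The 0.81 is therefore an upper case, not a stated consequence of the plan.

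**Institution.** The article says "The randomization will be performed on an institutional basis to prevent bias", but silence on stratifying the test by institution is analysis-plan detail and carries no weight here.

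**Conclusion.** The point holds in this form. Followed as written, the plan compares groups defined partly by treatment received and adherence, with B drawn from two randomizations at different times and C partly from none. The resulting log-rank test is not a randomized comparison.

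The possible gain for deferred CN is over upfront CN only. It requires grouping by surgery received, exclusion of deaths before surgery, or a baseline clock. Against ICIs only, no consistent advantage for CN can be claimed, and the pooled contrast on which the trial is sized may be biased against CN. The figures assume exponential survival, equal hazards in all groups, the plan's control hazard and an unknown mix of routes into B.

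**What to change.** - In the primary endpoint, replace 'patients receiving' with 'patients randomized to'.
- Keep every randomized patient in the primary OS analysis, whatever surgery or adherence followed. Make any per-protocol analysis a sensitivity analysis.
- Time OS and PFS from each patient's own randomization.
- Compare A with first-visit B, and post-induction B with post-induction randomized C. Do not pool the two B cohorts.
- Report never-randomized Group C patients separately and descriptively. They have no randomization date and no randomized comparator.
- Adjustment for baseline IMDC feature count (already collected, Table 1) or institution is optional. With so few patients, many strata would thin the data.

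**Cost.** No new data are needed, but this is more than a change of wording. No randomization contains both A and C, so the pooled A+B versus C contrast and its 80% power cannot be carried over. Sample size justification has to be restated for each randomized contrast. With the assumed 17 events after the second randomization, power at HR 0.37 is about 54%. The restatement should be made before outcomes by group are examined.

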### Recruitment and consent

Overall patient recruitment will be supervised at Severance Hospital, where the project leader and the research center are located, and each center will recruit patients under the guidance of Severance Hospital. A multidisciplinary team composed of urologists, medical oncologists, and radiologists will determine patient selection under strict inclusion and exclusion criteria and regularly update these criteria as necessary.

Patients diagnosed with synchronous mRCC with clear-cell components and no prior therapy will be recruited. The study information will be provided to the patients during the first consultation and asked for their participation the next day, giving them sufficient time to consider. During patient participation, the most current written informed consent approved by the Ethics Committee (Additional file 2) will be obtained before any project-specific assessment or procedure. No study-related activities will begin before the informed consent form is signed. The participants will be allowed to retire at any point during the study. This information is clearly stated in the consent form.

### Compensation

Although no compensation will be provided for patients in this study, future patients would benefit greatly. Participation will be voluntary, and the management of patients will comply with current standards of care.

### Patients

Patient selection is based on the following inclusion, dropout, and exclusion criteria.

#### Inclusion criteria

Core needle biopsy-proven metastatic renal cell carcinoma—only clear cell histologic subtypes are acceptable.Synchronous metastatic renal cell carcinoma with a primary tumor in the kidney.The patient must be willing to provide their human-derived materials.Age ≥ 19 years.Signed written informed consent must be obtained from all patients prior to any study-specific procedures.The patient must be willing and able to comply with the protocol.Measurable disease as per response evaluation criteria for solid tumors (RECIST) v 1.1.Life expectancy of greater than 4 months.Patients with more than one prognostic factor by the IMDC criteria (intermediate- or poor-risk group).Patients indicated nivolumab/ipilimumab, according to the recommendations by the national health authorities. The prescription of nivolumab/ipilimumab under the circumstances of the study is considered standard treatment.Karnofsky Performance status ≥ 70.Females with a negative serum pregnancy test unless childbearing potential can be otherwise excluded (postmenopausal, hysterectomy, or oophorectomy) and not lactating.Fertile women of childbearing potential (< 2 years after last menstruation) and men must use effective means of contraception (oral contraceptives, intrauterine contraceptive device, barrier method of contraception in conjunction with spermicidal jelly or surgical sterilization).The required laboratory values are as follows:Adequate bone marrow function (Absolute neutrophil count > 1500/mm3, platelets > 100 × 103/µl, hemoglobin > 10.0 g/dL)International normalized ratio (INR) ≤ 1.2 × upper limit of normal (ULN)Adequate hepatic function (bilirubin ≤ 1.5 × ULN, ALAT ≤ 2.5 × ULN)Adequate kidney function (eGFR > 35 mL/min)

#### Dropout criteria

If a subject fulfills any of the following dropout criteria, they will be discontinued from the middle of the study:

Patients who do not want to participate in the study.Patients who fall into the exclusion criteria during the study (such as the patients who need for starting systemic corticosteroids, antibiotics, investigational drugs, etc., during the study).Patients with severe side effects during the treatment and treatment can no longer be continued according to the schedule.Patients who do not adhere to the protocol of the study.

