### Sample size justification

Two prospective RCTs, PROBE (NCT04510597) and NORDICSUN (NCT03977571), are currently ongoing, but do not include an upfront CN arm. We determined the sample size based on the most recent real-world data that analyzed the intermediate/high risk group of mRCC patients stratified into upfront CN, deferred CN, and systemic treatment group [17]. To determine the required sample size for the study, we utilized two calculators for two-group survival analysis [18]. For Calculator 1, with a two-tailed alpha level (*α*) set at 0.05 and a beta level (*β*) of 0.2, along with a proportion of subjects in Group 1 (upfront and deferred CN) of 0.66 and a proportion in Group 0 (ICIs only) of 0.34, the relative hazard was set at 0.37. The calculated number of events needed to achieve 80% power was 35. For Calculator 2, with the total number of events set at 35, and assuming a baseline event rate of 0.53 and a median survival time in Group 0 (ICIs only) of 1.3 years, along with a censoring rate of 0.1 and a planned average length of follow-up of 5 years, the sample sizes required for each group were determined. Therefore, a total of 57 subjects were needed for the study.

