## Discussion

The optimal use of CN in mRCC settings remains unclear, especially in ICI therapy settings [19], where the most recent evidence has been generated in the TKI era [19]. Although the potential of CN in the primitive IO era has drawn attention, no studies have thoroughly evaluated the role of CN in ICI therapy in patients with mRCC, where recent guidelines have moved away from TKI monotherapy in favor of ICI-based combinations. This is the first study to comprehensively incorporate both upfront and deferred CN and compare both with ICI therapy, redefining the role and timing of surgeries in mRCC. Because oncologic surgery can effectively control cancer by removing tumor cells [20], it should be considered as a treatment option for mRCC in selected patients, weighing the benefits and risks tailored to each patient. Moreover, CN may reduce the cost of ICI therapy, allowing for therapeutic holidays [19]. As patient selection is critical for expanding the role of CN in the contemporary IO era [21], the objective of this study is to develop biomarkers for patient selection for CN by analyzing gene mutation profiles and microbiomes. Due to the small number of study population, there could be some difficulties in drawing conclusions for discovery of biomarkers. Therefore, we will first achieve our primary endpoint, OS, and will expand the study for other analysis. Furthermore, the decision to perform CN should be discussed by a multidisciplinary team and clearly explained to the patients during shared decision-making sessions.

This study was registered at ClinicalTrials.gov on March 3, 2023. Patient accrual began in December 2022. Follow-up will be performed for at least 5 years or until death.

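### The dropout rules take patients out of the study, not only off treatment, so overall survival is open to informative loss and may fall short of its planned deaths

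*Protocol article*

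**What the plan says.** The Dropout criteria of the protocol article state that a subject who meets any listed criterion leaves the study part-way. One criterion carries the exclusion criteria forward past enrolment, with examples: "such as the patients who need for starting systemic corticosteroids, antibiotics, investigational drugs, etc., during the study". Another is toxicity: "Patients with severe side effects during the treatment and treatment can no longer be continued according to the schedule". A third is failure to adhere to the protocol, and the section Adherence with study protocol repeats that such patients are dropped from the study.

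The Statistical analysis section adds that subjects without endpoints, or who violate the protocol, are excluded.

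Two other places bear on the same patients. The text below Fig. 1 (Study timeline) deals with stopping the drug: "Patients will discontinue ICI therapy when they develop serious adverse events, including grade 3 or worse". The Discussion gives the duration of follow-up: "Follow-up will be performed for at least 5 years or until death". It does not say whether this covers patients who have met a dropout criterion.

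The primary endpoint is overall survival.

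**The concern.** Survival can be observed whatever treatment a patient receives, so stopping treatment is no reason to stop recording deaths. Needing corticosteroids, needing antibiotics, severe toxicity and departing from the schedule are all consequences of the assigned treatment or of a worsening course. Patients who meet them probably have a different risk of death from those who do not. If follow-up ends there, the censoring is informative. If they are also excluded from analysis, the groups compared are no longer the groups that were randomised.

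The rate of removal may also differ between groups. All three receive the same immunotherapy, but only Groups A and B have surgery, and at different times. Events and deviations linked to surgery can therefore arise only in those two groups. A difference of that kind would bias the hazard ratio in a direction that cannot be predicted from the article.

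Two further things are at stake. Deaths and late toxicity after removal may be missed, although treatment-related adverse events are a secondary endpoint and the interim reviews concern safety. Deaths that the sample size relies on may also go unrecorded.

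**Working it through.** **Inputs** (Sample size justification, unless noted). Two-sided alpha 0.05 (two-sided tests are confirmed under Statistical analysis). "the relative hazard was set at 0.37". Allocation 0.66 (upfront and deferred nephrectomy pooled) to 0.34 (immunotherapy only). Baseline event rate 0.53, which as an annual hazard agrees with the 1.3-year median (ln 2 / 1.3 = 0.533). Censoring rate 0.1, average follow-up 5 years, total 57.

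**Step 1: the plan's event count.** "The calculated number of events needed to achieve 80% power was 35". Schoenfeld's formula gives D = (1.960 + 0.842)² / (0.66 × 0.34 × (ln 0.37)²) = 7.849 / (0.2244 × 0.9885) = 35.4. This agrees with 35. Power at 35 deaths is Φ(√(35 × 0.2244) × |ln 0.37| − 1.960) = 79.6%.

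**Step 2: the plan's total.** With death hazard λ, censoring hazard c per year and follow-up T, the probability of an observed death is P = λ/(λ+c) × (1 − exp(−(λ+c)T)).
- Immunotherapy only: λ = 0.53, P = 0.53/0.63 × (1 − exp(−3.15)) = 0.805.
- Nephrectomy: λ = 0.37 × 0.53 = 0.1961, P = 0.1961/0.2961 × (1 − exp(−1.4805)) = 0.512.
- Pooled: 0.34 × 0.805 + 0.66 × 0.512 = 0.611, and 35/0.6114 = 57.2.

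So 57 reproduces when 0.1 is an annual censoring hazard. No censoring gives 48, and a flat 10% loss gives 53. The 0.1 per year amounts to about 22% of patients lost before death over 5 years (15% immunotherapy only, 26% nephrectomy). Under it, 57 patients give 34.9 expected deaths, so nothing is spare.

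**Step 3: adding the dropout rules.** Suppose a share f of each group is removed, uniformly over months 0 to 6, and censored then. The article gives no rate, so f is an assumption. Averaged over that window, the chance that a removed patient's death is seen is 0.0715 pooled with c = 0.1, and 0.0726 with c = 0. For patients not removed it is 0.6114 with c = 0.1 and 0.7284 with c = 0. Then D = 57 × [(1 − f) × P + f × U], where P is the 5-year value and U the early one.
- f = 20%, removal on top of 0.1 per year: 57 × (0.8 × 0.6114 + 0.2 × 0.0715) = 28.7.
- f = 20%, dropout rules the only loss: 57 × (0.8 × 0.7284 + 0.2 × 0.0726) = 34.0.

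| Removed (assumed) | Added to 0.1/year: deaths, power | Only source of loss: deaths, power |
|---|---|---|
| 0% | 34.9, 79% | 41.5, 86% |
| 20% | 28.7, 71% | 34.0, 78.5% |
| 30% | 25.6, 66% | 30.3, 74% |
| 50% | 19.5, 55% | 22.8, 61% |

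In the right-hand scenario 35 deaths are still expected until f = (0.7284 − 35/57) / (0.7284 − 0.0726) = 0.174, or about 17%.

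These figures treat removal as uninformative and equal across groups. They measure lost events only and say nothing about bias, which is the main harm. The documents give no inputs from which to size the bias.

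**The case against.** The strongest reply is that the sample size already allows for loss. The planned 0.1 per year covers about 22% of patients, and removals under the dropout rules may be exactly what it was meant to cover. That stands. A reader might infer from the rules that the 35 deaths will not be reached, but no removal rate is given, and if these rules are the only loss the target holds up to about 17% removed.

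Arm dependence is likewise an inference. A reader might go further and argue that antibiotics around surgery would remove most operated patients and nobody in Group C for that reason. The article does not support that. It never mentions perioperative antibiotics, and the antibiotic exclusion criterion is tied to the 14 days before systemic therapy starts. The examples in the Dropout criteria are worded more broadly, but a fully literal carry-forward of the exclusion criteria cannot be intended: the exclusion for recent major surgery would remove every operated patient. What stands is that only two groups have surgery, so exposure to the triggers can differ.

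It can also be said that the text below Fig. 1 governs when the drug stops and the Dropout criteria govern who leaves, so the two need not contradict each other, and that the Discussion's follow-up statement has no exception for dropouts. Both are fair. The text is ambiguous rather than flatly contradictory. But the statements on leaving the study and on exclusion from analysis are explicit, and nothing shown says that dropouts remain in survival follow-up.

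Finally, toxicities and causes of discontinuation are recorded (Table 1), so it would be too much to say that toxicity is hidden. At most, what happens to a patient after removal may be missed.

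**Conclusion.** The concern holds as a defect in what the article states. Followed as written, the rules end participation for reasons related to treatment and prognosis, and may then exclude the same patients from the analysis of overall survival. The loss is likely to be informative, can bias the hazard ratio, and may differ by arm. This should be corrected before more follow-up is forgone, because survival data not collected may not be recoverable.

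The effect on the event count is conditional. For 20% to 50% early removal, power runs from 71% down to 55% if removal adds to the planned censoring, and from 78.5% down to 61% if it replaces it. These figures rest on the plan's own hazards, a pooled comparison of nephrectomy with immunotherapy alone, removal spread evenly over 6 months, and assumed removal shares. A definite shortfall, or a definite difference in removal between arms, is not established.

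**What to change.** Amend the protocol so that stopping study treatment and leaving the study are separate events.

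- Only withdrawal of consent or true loss to follow-up ends survival and toxicity follow-up. Patients who start corticosteroids or antibiotics, stop for toxicity or deviate from the protocol stay in follow-up.
- All randomised patients are analysed as randomised. For the primary overall survival analysis, remove the exclusion of protocol violators and of subjects without endpoints; patients without an observed death are censored at last contact. A per-protocol analysis may be kept as secondary.
- Corticosteroid or antibiotic use is flagged for a sensitivity analysis of the microbiome data.
- Reconcile the Dropout criteria, the treatment-stopping text below Fig. 1, the Statistical analysis exclusion, Adherence with study protocol, and the follow-up statement in the Discussion. Changing the first without the Statistical analysis section would leave patients followed and then excluded.

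The amendment should be confined to study participation, follow-up and analysis. It should not alter any clinical rule on when treatment stops.

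The cost is a short amendment and survival-status checks for patients off treatment. With recruitment planned to December 2027, it can still cover most of the follow-up.
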